**Methods:**

Eligible and consenting smokers (*n* = 2550) who call a telephone quitline will be randomized to one of three groups; the standard quitline or standard quitline plus a weight management program added either simultaneously or sequentially to the tobacco program. The study aims to test: 1) the effectiveness of the combined intervention on smoking cessation and weight, 2) the cost-effectiveness of the combined intervention on cessation and weight and 3) theoretically pre-specified mediators of treatment effects on cessation: reduced weight concerns, increased outcome expectancies about quitting and improved self-efficacy about quitting without weight gain.

Baseline, 6 month and 12 month data will be analyzed using multivariate statistical analyses and groups will be compared on treatment adherence, quit rates and change in weight among abstinent participants. To determine if the association between group assignment and primary outcomes (30-day abstinence and change in weight at 6 months) is moderated by pre-determined baseline and process measures, interaction terms will be included in the regression models and their significance assessed.

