## Background

### Comorbid smoking and obesity are a public health problem

Obesity and smoking account for over three quarters of a million deaths per year in the U.S. [1–3] and about 92 % of smokers have at least one additional health risk behavior [4–8]. More than nine million adults are both obese and smoke [9], markedly increasing their mortality risk [2, 3]. Although effective smoking cessation treatments are available [10–13], weight gain following cessation is common [14–18]. Modest weight gain of about 8-10 lb is the norm, but some smokers gain more than 20 lb after quitting. There is evidence that obese smokers and smokers concerned about post-cessation weight gain may experience greater than average weight gain after quitting and cessation related weight gain can increase the risk for weight related health conditions [16, 19–24]. A systematic review of interventions focused on preventing post cessation weight gain confirmed prior research findings that 80–90 % of smokers gain weight after quitting; that only 10–20 % gain more than 10 kg and that the weight gain is generally permanent unless changes in lifestyle are adopted [25]. The authors concluded that there are very few interventions that entirely prevent post cessation weight gain, but there is evidence of modest effects for reducing the amount of weight gained.

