### Measures

Data for analyses will come from information collected when a person registers with the quitline, baseline data collected by a quit coach, 6 and 12 month phone or on-line follow-up data collected by a survey team and Alere’s tracking information on number and duration of counseling calls completed.

**Primary outcome measures** will be self-reported 30-day point prevalent abstinence and self-reported change in weight at 6 months.

**Secondary outcome measures** include 7-day point prevalence and continuous abstinence at 6 and 12 months, and reduction in amount smoked in continuing smokers. Other data will include descriptive and process data for analyses of mediators and moderators of intervention effects and cost data.

Survey content will be derived from standardized validated measures used to assess tobacco history, weight variables and outcomes, and from prior research findings and theoretical underpinnings of efficacious clinical trials [27, 33, 34, 37, 40, 50]. Most of the following measures will be assessed at baseline and/or 6 & 12 months and used to describe participants and evaluate outcomes.

*Demographics:* age, gender, race, ethnicity, education, height, weight, and other general demographics.

*Chronic Disease:* assessed by asking participants if they have ever been diagnosed with diabetes, heart disease, asthma, or a lung disease.

*Depressive symptoms:* measured with the PHQ-2, a 2 item screening measure for depressive symptoms that has demonstrated strong criterion and construct validity. The scale uses a 4-point response option to assess frequency of dysphoria and anhedonia. Sensitivity of the PHQ-2 has been reported at 84 %, with 72 % specificity for a cut score of 3 [51].

*Perceived stress:* measured with the 4-item Perceived Stress Scale (PSS), to assess the degree to which respondents find their lives to be stressful. The PSS has been shown to be a valid and reliable measure with alpha reliability coefficients from .84 to .86 [52]. PSS scores have been shown to be related to smoking relapse [53].

*Smoking/quit attempt history:* lifetime and current smoking, cigarettes smoked per day, history of quit attempts, prior use of nicotine replacement and other cessation treatments, and exposure to other household users.

*Nicotine dependence:* Fagerström Test of Nicotine Dependence (FTND) [54], which is the most commonly used measure for assessing nicotine dependence and is predictive of abstinence [55].

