### Statistical analysis plan

*Aim 1.* The primary cessation and weight change outcomes will be assessed at 6 months and the secondary outcomes at 12 months. We hypothesize that combined treatments will be more effective than standard treatment and that sequential treatment will be more effective than simultaneous treatment for increasing quit rates or reducing weight gain, without harming the other outcome. The primary analysis approach for testing the effectiveness of the combined treatments on cessation will be logistic regression with an indicator for the main effect of treatment and an interaction term to account for the difference in treatment effectiveness of the two treatments. The regression equation will also include baseline characteristics that are predictive of abstinence (age, gender, etc.) and an indicator of whether the participant is qualified for receiving NRT through their State quitline plan. Analyses of cessation will be conducted three ways: 1) using multiply imputed values for missing cessation status; 2) on the set of responders to follow-up (ie, those for whom we know the cessation outcome), 3) assuming that non-responders (lost to follow-up) have relapsed. We will also conduct sensitivity analyses for missing cessation results by reanalyzing the data with different assumed probabilities of relapse. The primary analysis approach for testing the effectiveness of the combined treatments on weight will be linear regression. The regressions will include an indicator for the main effect of treatment, an interaction term to account for differences in treatment effectiveness, current cessation status and the interaction of treatment group and current cessation status as covariates, thus allowing estimates of weight gain for all participants and (as secondary analyses) for quitters and smokers. A regression approach that is robust to heterogeneity in variance will be used. We will address missing values using multiple imputation as well as conducting sensitivity analyses with different assumed amounts of weight gain for non-responders to determine how extreme such weight gains (or differential weight gains among non-responders in different groups) would need to be to invalidate statistically significant results.

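### The primary weight regression conditions on follow-up smoking status, and the article names no contrast from it that gives the randomised effect on weight

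*Protocol article*

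**What the plan says.** All places are in the Protocol article.

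- **Measures** names the primary outcomes as "self-reported 30-day point prevalent abstinence and self-reported change in weight at 6 months", with no restriction of weight change to any subgroup.
- **Statistical analysis plan, Aim 1** states: "The primary analysis approach for testing the effectiveness of the combined treatments on weight will be linear regression". That regression contains a treatment indicator, a term separating the two combined treatments, and "current cessation status and the interaction of treatment group and current cessation status as covariates". The stated purpose is "thus allowing estimates of weight gain for all participants and (as secondary analyses) for quitters and smokers". No primary weight model without the status terms is named.
- **Aim 1** also gives the hypothesis: combined treatment is expected to do better than standard care "for increasing quit rates or reducing weight gain, without harming the other outcome".
- **Aim 2** divides the added programme cost by the difference in weight gain between the standard and combined groups, which is a plain difference between arms.
- **Abstract, Methods** says that "groups will be compared on treatment adherence, quit rates and change in weight among abstinent participants". Its next sentence names 6-month weight change as a primary outcome without that limit.

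**The concern.** Everyone smokes at entry (10 or more cigarettes a day), so current cessation status can only be a follow-up status. The article supplies both links that make it a problem as a covariate. Treatment is expected to change it: the trial is powered on a difference in quitting. It also changes weight: "Modest weight gain of about 8-10 lb is the norm, but some smokers gain more than 20 lb after quitting". A model that holds it fixed therefore removes one route by which treatment affects weight.

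The Background adds that weight gain can interfere with quitting, and Aim 3 lists weight change as a possible mediator of cessation. Quitters in one arm may therefore differ from quitters in another in their tendency to gain weight, and randomisation does not protect comparisons within status groups.

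At stake is what the primary weight result means. If a coefficient from this model is reported as the treatment effect, it need not equal the difference between randomised arms. It also need not match the weight difference used in the Aim 2 cost per pound not gained.

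**Working it through.** **Inputs from the article (Sample size and power analysis).** 850 per group, so 850 standard care against 1,700 combined. The abstinence rate is 29.6% for employer and health plan clients and 20% for state quitlines. The detectable difference is 5.7 points (odds ratio 1.30) for combined against standard.

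**Reproducing the plan's figure.** 29.6% + 5.7 points = 35.3%. The odds ratio is (0.353/0.647)/(0.296/0.704) = 1.298, which agrees with 1.30. The article gives no power or target difference for weight.

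**Assumption.** Let *g* be the extra weight gain of quitters over continuing smokers in the standard arm. The article does not give it. Its usual post-cessation gain of 8-10 lb is 3.6-4.5 kg (at 0.4536 kg per lb), so 4 kg is used, with a range of 2-6 kg.

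**Formulas.** Let p0 = 0.296 and p1 = 0.353. Let dq and ds be the direct treatment effects on weight in quitters and smokers.

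- Randomised effect = p1(g + dq) + (1 - p1)ds - p0·g
- Coefficient with smokers as reference (0/1 coding) = ds
- Average over pooled status = P·dq + (1 - P)ds, where P = (850 × 0.296 + 1,700 × 0.353)/2,550 = 0.334

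**Results (kg).**

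| Case | Randomised effect | Coefficient, smokers as reference | Pooled-status average |
|---|---|---|---|
| No direct effect, g = 2 / 4 / 6 | +0.114 / +0.228 / +0.342 | 0 | 0 |
| -1 in both groups, g = 2 / 4 / 6 | -0.886 / -0.772 / -0.658 | -1 | -1 |
| -1 in quitters only, g = 4 | 0.353 × 3 - 0.296 × 4 = -0.125 | 0 | -0.334 |
| -1 in quitters only, equal quit rates of 29.6% | -0.296 | 0 | -0.296 |

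With equal direct effects the discrepancy is (p1 - p0) × g = 0.057 × 2, 4 or 6 = 0.114, 0.228 or 0.342 kg. Only the difference in quit rates enters, so a 20% control rate gives the same values. When treatment raises quitting, the conditional estimate makes the programme look better on weight than the randomised comparison does.

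**Averaging each arm over its own quit rate.** In a model containing only arm, status and their interaction, each fitted cell is the observed cell mean. Weighting an arm's two cells by that arm's own quit rate returns the arm mean. The contrast is then the unadjusted arm difference.

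**Simulation.** 600 replicates, 850 against 1,700, g = 4 kg, no direct effect, an assumed unmeasured cause of both quitting and weight gain, and a residual SD of about 4.3 kg (assumed). The true randomised effect is 0.228 kg. Mean estimates:

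- unadjusted arm difference: 0.233 kg
- treatment coefficient in the planned model: 0.059 kg
- pooled-status average: 0.069 kg
- each arm averaged over its own quit rate: 0.233 kg

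The direct effect was set to zero, so the 0.06-0.07 kg left in the conditional estimates comes from selection into the status groups.

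**The case against.** **The text aims at all participants.** Aim 1 says the model serves all participants and already calls the quitter and smoker estimates secondary. This stands. A reader might infer that no estimate from this model can be the randomised effect. That goes too far, because averaging each arm over its own quit rate recovers it exactly, and when quit rates are equal the pooled average does too. But the article does not state the own-arm averaging, and where it is used the status terms add nothing to the primary estimate.

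**A condensed article may leave the contrast to the analysis plan.** True of the contrast. The covariates are another matter: the article itself fixes them for the primary model.

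**Coding is not stated.** This also stands. A reader might infer that a benefit confined to quitters would be missed altogether. That follows only if status is coded 0/1 and the main effect is read alone. In the last row of the table, the status average gives the full -0.296 kg.

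**The terms have a purpose.** Quitting usually brings weight gain, so an unadjusted comparison can make an arm that produces more quitters look worse on weight. Weight gain given smoking status is a sensible question for a programme aimed at post-cessation gain. It is a secondary question here, because Measures, Aim 1 and Aim 2 all point to the effect by arm in all participants. Cessation is reported beside weight as the other primary outcome, so the trade-off remains visible.

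**The abstract.** A reader might infer that it redefines the primary weight outcome as weight change in abstinent participants. Its next sentence does not support that. This is loose wording.

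**Conclusion.** The concern holds in a limited form. The stated primary weight model conditions on a variable that arises after randomisation and that treatment is expected to change, and no contrast that recovers the randomised effect is named. Read directly or averaged over pooled status, its treatment estimate departs from the randomised effect by about 0.11-0.34 kg, and by 0.23 kg at a 4 kg gap. Those figures assume a 5.7-point difference in quitting, an equal direct effect in both status groups, and a quitter-smoker gap of 2-6 kg, which the article does not supply. For the pooled average the discrepancy vanishes if quit rates do not differ by arm. For a coefficient read at a reference status it can remain even then, if the direct effect differs between quitters and smokers.

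The size of any selection bias within status groups cannot be derived from the article. The simulation shows that it can arise, but its parameters are assumed. With no target difference for weight in the article, the discrepancy cannot be set against a planned effect. It matters because it affects the interpretation of a primary outcome and is simple to remove.

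**What to change.** - **Primary weight analysis:** regress 6-month weight change on randomised arm in all randomised participants, keeping the planned combined-treatment indicator and the term separating the two combined treatments. Adjust for baseline covariates only. Keep the planned multiple imputation and the variance-robust approach.
- **Secondary analyses:** keep the model with cessation status and its interaction for the quitter and smoker estimates already called secondary, and label them as non-randomised comparisons.
- **Abstract:** bring the phrase about weight change in abstinent participants into line with the unrestricted primary outcome in Measures.

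The cost is analysis wording only. No new data are needed and the sample size does not change.

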*Outcome expectations for success at smoking cessation and weight control:* single-item 10-point scales to rate participants’ expectations about the degree to which treatment would (a) help them quit smoking, (b) minimize weight gain, and (c) be effective overall. In the original efficacy trial [27], one-month test–retest reliabilities for these single-item scales ranged as follows: .36–.71 for outcome expectations about quitting smoking, .42–.59 for expectations about minimizing weight gain, and .34–.74 for expectations about the program overall, with ratings showing increased reliability later in treatment. Data from the original efficacy trial indicates that adding weight management increased outcome expectations for abstinence [27]. We will assess whether groups are similar at baseline on these measures and will evaluate these measures in mediator analyses.

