To test whether changes attributable to the weight management program mediate the cessation rate, we will examine changes in weight concerns, weight, outcome expectancies on quitting, and self-efficacy in quitting without weight gain. Mediation implies a causal hypothesis whereby an independent variable (ie, the weight management program) causes a mediator (eg, reduced weight concerns) that causes a change in a dependent variable (ie, cessation) [64]. We will follow four steps to test mediation effects [65, 66]. For example, to assess whether reduced weight concerns mediates cessation, we must: (1) demonstrate significantly different cessation outcomes for weight management and comparison groups, (2) demonstrate differences in weight concerns by condition, (3) establish that reduced weight concerns is significantly related to cessation rate, and (4) show that the effect of a weight management intervention on cessation rate is significantly less after controlling for change in weight concerns. We will further test whether changes in outcomes expectancies of treatment on quitting, self-efficacy in quitting without weight gain, physical activity and diet (eg fruits and vegetables) mediate the effect of the weight management program on weight gain. Regression analyses will be conducted to examine the moderating effects on cessation and weight gain of baseline characteristics of BMI, age, gender, weight concerns, nicotine dependence, outcome expectancies and self-efficacy in quitting. Moderators will be included in the regression analyses as mean-centered covariates and as interaction terms with the combined treatment group indicator.

Exploratory analyses will also assess mediators of weight gain and whether baseline BMI, weight concerns, self-efficacy, outcome expectancies, nicotine dependence, use of medications, age and gender moderate the effectiveness of the different interventions for cessation and weight outcomes.

All analyses will be conducted using SAS or STATA software.

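### The Aim 3 mediators are described as changes with no baseline-adjusted model named; a change score is less precise than a baseline-adjusted follow-up rating and can halve the mediator-cessation slope

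*Protocol article*

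**What the plan says.** The Statistical analysis plan (Aim 3) introduces the mediators of cessation with "we will examine changes in weight concerns, weight, outcome expectancies on quitting, and self-efficacy in quitting without weight gain". It then sets out four steps, using weight concerns as the worked example. Step 2 is to "demonstrate differences in weight concerns by condition". Step 4 is to show that the treatment effect is "significantly less after controlling for change in weight concerns". A second set of mediation tests, for weight gain, is worded the same way: "We will further test whether changes in outcomes expectancies of treatment on quitting, self-efficacy in quitting without weight gain, physical activity and diet". No baseline-adjusted mediator model is named.

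Under Measures, outcome expectations are single-item 10-point ratings. Groups are to be compared on them at baseline, so a baseline rating exists. The same paragraph gives one-month test-retest reliabilities from the original efficacy trial: .36 to .71 for quitting, .42 to .59 for minimising weight gain and .34 to .74 for the programme overall, "with ratings showing increased reliability later in treatment". The correlation between baseline and follow-up ratings in this trial is not given.

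**The concern.** The natural reading is that each mediator is follow-up minus baseline. Randomisation already balances the baseline rating in expectation, so the only reason to use it in the arm comparison is to remove noise. Subtracting it in full is the best use of it only when r is 1. For a single-item rating with modest stability, full subtraction removes too much and carries the baseline's own noise into the result.

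Two parts of Aim 3 are exposed. Step 2 asks whether treatment moved the mediator, and it loses precision. Steps 3 and 4 ask whether the mediator relates to cessation and accounts for the treatment effect. There the change score imposes a constraint on the coefficients that can shrink the association. Each step must succeed for mediation to be claimed, so the losses compound. Mediation is one of the trial's three aims, and outcome expectancies about quitting are one of the three mediators named in the abstract.

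**Working it through.** **Inputs from the protocol article.** 850 participants per group (Sample size and power analysis), so 850 standard care against 1,700 combined treatment. One-month test-retest values of .36 to .71 for expectations about quitting (Measures). The article states no power or precision for the mediator analysis, so there is no figure of its own to reproduce.

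**Assumptions.** r is not stated; the range .36 to .71 stands in for it. SDs are equal at both times and set to 1. Response is full, and the test is two-sided at 5%.

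**Step 2: variance of the mediator, per participant**
- Follow-up alone: 1
- Change score: 2(1 − r)
- Follow-up adjusted for baseline: 1 − r²
- Ratio, change to adjusted: 2(1 − r)/(1 − r²) = 2/(1 + r)
- Share of participants in effect discarded: 1 − (1 + r)/2 = (1 − r)/2

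| r | Change | Follow-up alone | Adjusted | Ratio change/adjusted | Share discarded |
|---|---|---|---|---|---|
| .36 | 1.28 | 1.00 | 0.87 | 1.47 | 32% |
| .50 | 1.00 | 1.00 | 0.75 | 1.33 | 25% |
| .71 | 0.58 | 1.00 | 0.50 | 1.17 | 14.5% |

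The change score equals follow-up alone when 2(1 − r) = 1, that is at r = .50. Below that it is noisier; above that it is more precise. Against baseline adjustment it is less precise at every r below 1.

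**The same in power.** Take the arm difference that follow-up alone detects with 80% power: (1.96 + 0.84) × √(1/850 + 1/1,700) = 0.118 SD. This size is illustrative; the protocol gives no expected mediator effect.

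| r | Change | Follow-up alone | Adjusted |
|---|---|---|---|
| .36 | 69.7% | 80% | 85.2% |
| .50 | 80% | 80% | 89.9% |
| .71 | 95.7% | 80% | 97.8% |

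**Steps 3 and 4: the slope.** Let F be the follow-up rating and B the baseline rating, and suppose the log-odds of cessation depend on F with slope b. On a linear scale, regressing on D = F − B gives

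slope = b × cov(F, D)/var(D) = b(1 − r)/[2(1 − r)] = b/2,

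whatever the value of r. A logistic simulation with b = 0.30 agrees: the slope on D came out at about 0.15 at r = .36, .50 and .71, while the model with both F and B returned about 0.30 for F. Because randomisation makes the expected arm difference in D the same as in F, a halved slope means that roughly half the mediated effect is credited to the mediator in step 4.

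The model with F and B contains the change-score model as the special case in which the two coefficients are equal and opposite. If true change is what drives quitting, it still recovers that.

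**The case against.** The strongest objection is that the article never writes out a subtraction for expectancies. For reduction in smoking and for weight gain, Measures defines a difference between baseline and follow-up; for expectancies it does not. Step 2 speaks only of differences by condition. Controlling for change could be carried out by entering follow-up and baseline together, and a separate analysis plan may do so. This stands as a limit: the change score is the natural reading, not a written formula. But the mediators are repeatedly called changes and no adjusted model is named, so the wording should be settled either way.

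Several stronger readings are tempting, and the document does not support them:
- *That subtraction is always worse than ignoring baseline.* This is true only below r = .50, and the quoted range reaches .71, where the change score is clearly better than follow-up alone.
- *That .36 is this trial's correlation.* The values are one-month figures from the earlier trial, which the Discussion describes as in-person and group-based. A longer interval makes a higher value unlikely, but that is a judgement. Low retest values may also reflect real change in expectations.
- *That the baseline rating is the least reliable one.* Reliability is said to rise later in treatment, but the article does not say which interval gave the lowest value or whether a pre-treatment rating was among them.
- *That a null result for expectancies would be only an artefact.* At .71 the power loss against adjustment is about 2 points, and a larger mediator effect would be detected either way.

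It is also fair to say that no reliability figure is given for weight concerns or self-efficacy. The advantage of adjustment does not depend on one, since it holds at every r below 1, but its size for those measures is unknown.

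**Conclusion.** The point holds as a matter of precision and attenuation in the Aim 3 mediation tests. With equal SDs, the change score is less precise than the baseline-adjusted follow-up rating at every r below 1. If r lies between .36 and .71, the variance ratio is 1.47 to 1.17. The halving of the slope does not depend on r, but it does depend on cessation following the follow-up level of the mediator; if cessation follows true change, the change score is not penalised in this way. The step 2 arm comparison loses precision but is not biased. The primary cessation and weight outcomes are unaffected, and the mediation of cessation is pursued only if step 1 shows a cessation effect. It is worth correcting because the improvement uses data already planned for collection.

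**What to change.** In Aim 3, state that the mediator is the follow-up rating with its baseline value as a covariate, in both the mediator model (step 2) and the cessation model (steps 3 and 4), in place of the change score. Apply this to outcome expectancies, weight concerns and self-efficacy. If an analysis plan already does this, bring the article's description into line with it.

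The cost is a change of wording and one extra covariate per model; no new data are needed. A sensitivity analysis that corrects the mediator-cessation slope for measurement error is optional and not part of the fix. If it is done, correcting the follow-up rating for a reliability as low as .36 would be poorly supported, since the article says reliability rises later in treatment.

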Process data will be collected using Alere Wellbeing’s automated call tracking system and stored in a secure system. Outcome data will be collected 6 and 12 months after randomization (see Fig. 1: Study Design). We will collect outcome data via surveys administered first by email, then phone, then mailed, for all participants randomized into the study and who do not withdraw consent for follow-up. Strategies to promote follow-up completion include incentives for completing surveys, $2 pre-incentives sent with mailed surveys, and an additional incentive for completing the 12-month email survey within 72 h. Telephone outcome assessors, who will receive specialized training on the study, will be blinded to the intervention assignment. All outcome survey data will be collected via a secure link to DatStat, a survey collection database.

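### Aim 3 tests mediation only after a significant total effect on cessation, names no test of the indirect effect, and describes survey times that can make a mediator a consequence of quitting

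*Protocol article*

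**What the plan says.** The Statistical analysis plan section of the protocol article treats mediation as a causal hypothesis and commits to the method: "We will follow four steps to test mediation effects". The worked example, weight concerns, presents all four steps as requirements. Step 1 is to "demonstrate significantly different cessation outcomes for weight management and comparison groups". Steps 2 and 3 ask that the mediator differ by condition and be related to cessation. Step 4 is to "show that the effect of a weight management intervention on cessation rate is significantly less after controlling for change in weight concerns". The candidate mediators are listed thus: "we will examine changes in weight concerns, weight, outcome expectancies on quitting, and self-efficacy in quitting without weight gain". No estimate or test of the indirect effect is named, and no time points are assigned to mediator and outcome.

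On timing, the Study design section says "Outcome data will be collected 6 and 12 months after randomization", and the Measures section says "Most of the following measures will be assessed at baseline and/or 6 & 12 months". No interim survey is described. Weight is also taken at counselling calls, but this is described for the weight program only.

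**The concern.** A mediator can carry an effect on quitting even when the total effect is not significant. The total effect may be real but small, or a helpful path (less concern about weight) may be offset by a harmful one (for example, added burden). The abstract itself leaves open whether the added program helps or harms quitting. Under the gate, Aim 3 would then end without examining the paths that could explain the result.

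The second issue is direction. Concern about weight gain after quitting, and weight change itself, can both follow from having quit. If they are measured in the same survey as abstinence, a regression cannot tell a cause of quitting from a result of it. Mediation is one of the study's three stated aims, so both problems bear on a headline conclusion, though not on the primary outcomes.

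**Working it through.** **Inputs.** From Sample size and power analysis: 850 per group, hence 850 v 1,700 for control v combined; 6-month control abstinence 29.6% (commercial) or 20% (state); detectable difference 5.7 points, OR 1.30, 80% power by Fisher's exact test; 2.5 points called clinically significant. That section states no alpha; two-sided 0.05 is assumed. The article gives no path strengths, so those below are assumptions.

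**1. The plan's own figure.** Exact enumeration of Fisher's test at 29.6% v 35.3% gives 81.4% (doubled tail) or 82.0% (minimum likelihood). The stated 80% is reproduced. The stated difference and OR fit together only at the 29.6% rate.

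**2. Power of the step 1 gate.** Power = Φ[(d − 1.96·s0)/s1], where s0 = √[p̄(1−p̄)(1/850 + 1/1700)] and s1 = √[p1(1−p1)/850 + p2(1−p2)/1700].

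- d = 0.025: p̄ = 0.3127, s0 = 0.01947, s1 = 0.01932. (0.025 − 0.03817)/0.01932 = −0.68, so power is 25%.
- d = 0.057: p̄ = 0.334, s0 = 0.01981, s1 = 0.01948. (0.057 − 0.03883)/0.01948 = 0.93, so power is 82%.
- Same formula: 17.5% at 2 points, 33% at 3, 53% at 4.
- One combined arm v control (850 v 850): 20% at 2.5 points, 71% at 5.7.
- Control rate 20%, d = 0.025: s0 = 0.01731, s1 = 0.01705. (0.025 − 0.03392)/0.01705 = −0.52, so power is 30%.

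**3. What the gate discards when mediation is real.** Simulation, N = 2,550, 600 to 1,500 trials per scenario. Mediator M = a·T + noise (SD 1); logit P(quit) = constant + b·M + d·T. Steps 1 to 3 are compared with joint significance of the two paths (steps 2 and 3 without step 1).

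| a (SD) | b (log OR per SD) | direct effect d | total effect (points) | steps 1–3 | joint test |
|---|---|---|---|---|---|
| 0.2 | 0.3 | 0 | 1.2 | 10% | 99.7% |
| 0.2 | 0.5 | 0 | 2.0 | 19% | 99.7% |
| 0.3 | 0.5 | 0 | 3.1 | 34% | 100% |
| 0.3 | 0.9 | 0 | 5.1 | 73% | 100% |
| 0.55 | 0.5 | 0 | 5.7 | 83% | 100% |
| 0.3 | 0.5 | −0.15 | 0.0 | 5% | 100% |

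**4. Consequence of quitting read as a mediator.** Here the mediator has no effect on quitting. Abstinence is 29.6% v 35.3%, and M = a·T + k·(quit) + noise. With a = 0.2 and k = 0.3 to 0.5, steps 1 to 3 with a smaller adjusted coefficient pass in about 81% to 83% of trials. The treatment log OR falls from about 0.26 to 0.20 (k = 0.3) or 0.16 (k = 0.5), which looks like partial mediation.

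**5. Does a lag cure this?** Assume 75% of 6-month quitters and 6% of others are abstinent at 12 months. For controls this gives 0.296 × 0.75 + 0.704 × 0.06 = 26.4%, close to the 26.6% implied by the article's 3-point fall. Relating the 6-month mediator to 12-month abstinence without adjusting for 6-month status, the joint test is falsely positive in 12% to 24% of trials when only quitting moves the mediator (0.5 to 1 SD), and in about 100% when the program moves it too. Adjusting for 6-month abstinence brings this to about 5% or less.

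**The case against.** Aim 3 is framed as explaining treatment effects on cessation, so asking first for such an effect is coherent, and at the design effect of 5.7 points the gate usually opens. An article may also leave the pairing of mediator and outcome times to a fuller plan; a 6-to-12-month model is not excluded, and weight has call-level records. These points stand as limits: the gate can miss mediation rather than will miss it, and same-survey measurement is an inference for most mediators. They do not remove the explicit gate or the absence of a test of the indirect effect. Call-level weights are described only for the weight program and are not assigned to the mediation analysis.

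Three stronger readings are tempting and are not supported.

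- *The four steps report false mediation whenever quitting moves the mediator.* If quitting is the only thing that moves it, steps 1 to 3 pass in 5% to 8% of trials (shift 0.3 to 0.5 SD) and in 23% to 37% (1.0 to 1.5 SD). The treatment coefficient does not shrink on average (0.26 v 0.26), so step 4, which requires a significant reduction, would not generally be met.
- *Step 4 is invalid because odds ratios are non-collapsible.* Logistic regression is stated for Aim 1 ("The primary analysis approach for testing the effectiveness of the combined treatments on cessation will be logistic regression"), and no scale is named for step 4. At b = 0.3 to 0.5 the distortion is at most about 0.013 in log odds. For a strong predictor it moves the effect away from the null, which hides mediation rather than creating it.
- *Aim 3 stops whenever the primary 6-month test is negative.* Step 1 is not tied to that test, and mediation of weight gain is planned as well.

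**Conclusion.** The point holds in limited form. The gate on a significant total effect is explicit. At 2.5 points it passes about 25% of the time (30% at the state-quitline control rate), against about 82% at 5.7 points, and about 5% when opposing paths cancel. Any Benjamini-Hochberg adjustment of step 1 would lower these figures: about 17% at 2.5 points if 0.025 were needed. With the survey times described, a same-survey mediation result for 6-month cessation cannot bear a causal reading. The 81% to 83% figure depends on the program moving the mediator directly and in the same direction as quitting does. The results rest on two-sided 0.05, the full 2,550 analysed, and assumed path strengths. This is a weakness in one of the three stated aims that should be corrected; it does not affect the primary comparisons.

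**What to change.** - Remove step 1 as a requirement, and replace step 4 with a direct estimate of the indirect effect (product of coefficients, or natural indirect effect on the risk-difference scale) with a bootstrap 95% CI.
- For causal statements, relate the 6-month change in the mediator to 12-month abstinence, adjusting for the baseline mediator, baseline covariates and 6-month abstinence status. The last adjustment is essential: dropping the steps and adding a lag without it leaves the false-positive rates shown above.
- Report same-survey 6-month models, including those for weight change, as associations only.

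Cost: analysis wording only, since both surveys are already planned. The lagged analysis answers a narrower question, later abstinence given 6-month status. It loses some 12-month responders and excludes any mediation that acts before 6 months.
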